## Abstract

**Background:**

Suicide is among the top 10 leading causes of death worldwide. Of people who died by suicide, the majority are diagnosed with depression. It is estimated that 25%-60% of people with bipolar depression (BD) will attempt suicide at least once, and 10%-15% will die by suicide. Several treatments, such as lithium, clozapine, electroconvulsive therapy, and cognitive behavioral therapy, have been shown to be effective in treating suicidality. However, these treatments can be difficult to tolerate or may take months to take effect. Ketamine, a glutamate N-methyl-D-aspartate antagonist, has been shown to have rapid antisuicidal effect and antidepressant qualities, and is thus a promising intervention to target acute suicidality in patients with BD. However, the biological mechanism underlying its therapeutic action remains poorly understood. Enhancing our understanding of underlying mechanisms of action for ketamine’s effectiveness in reducing suicidality is critical to establishing biological markers of treatment response and developing tailored, personalized interventions for patients with BD.

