## Introduction

### Background and Rationale

Suicide is among the top 10 leading causes of death, with progressively increasing rates and is a critical public health issue [1]. Bipolar depression (BD) is a serious psychiatric condition with a high mortality rate due to suicide [2]. Between 25% and 60% of those with BD will attempt suicide at least once, and 10%-15% will die by suicide [3-5]. Several interventions, such as lithium, clozapine, electroconvulsive therapy, and cognitive behavioral therapy, have demonstrated antisuicidal properties [4,5]. However, as polypharmacy is common in patients with bipolar illness [6], adding another treatment can be difficult to tolerate, or new treatments may take months to take effect. Therefore, there is an urgent need to develop robust interventions to treat suicidality in patients with BD rapidly. In addition, establishing biological markers of treatment response is critical in developing personalized, tailored treatment interventions.

A paradigm shift from a monoamine hypothesis to a plasticity-based hypothesis of depression represents a substantial advancement, where accumulating evidence suggests that glutamatergic or excitatory neurotransmission system dysfunction plays a pivotal role in depression [7-9]. There are 3 classes of glutamate-gated ion channels such as α-amino-3-hydroxy-5-methyl-4-isoxazole propionic acid, and kainite and *N*-methyl-d-aspartate (NMDA) receptors that transduce the postsynaptic signal [7]. NMDA receptors are distributed throughout the brain and are fundamental to excitatory neurotransmission and the normal functioning of the central nervous system (CNS) [7,8]. Ketamine is the first clinically used NMDA receptor antagonist with a primary mechanism of action closely linked to the blockade of the NMDA receptor at the phencyclidine site, which mediates excitatory synaptic transmission through the CNS [8-10].

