### Data Collection Methods

Data will be collected on a baseline assessment, weekly during the course of IV ketamine, within a week after the completion of the intervention, and following 4 weeks for a final follow-up. Assessments will include psychiatric assessment, physical examination, and clinical assessments through manualized validated clinical scales (Multimedia Appendices 1 and 2).

*Psychiatric assessment* will include a consultation with a study physician to confirm a diagnosis. Demographic information, medical and psychiatric history, and concomitant medications will also be included.

A *physical examination* will include a physical exam performed by a study physician or a delegate, and blood work and electrocardiography for medical clearance according to standard clinical procedures also be reviewed by the study physician. Blood tests will include complete blood count with differential tests (white blood cells, red blood cells, hemoglobin, hematocrit, mean corpuscular volume, mean corpuscular hemoglobin, mean corpuscular hemoglobin concentration, red cell distribution width, mean platelet volume, platelet, nucleated red blood cell count, neutrophil count, lymphocyte count, monocyte count, eosinophil count, basophil count); blood chemistry test, including liver function (alanine transaminase and aspartate transaminase), kidney function (blood urea nitrogen and creatinine), and electrolytes (sodium, potassium, chloride, and phosphate); and thyroid function (thyroid-stimulating hormone). Study participants’ blood pressure will also be monitored before, during, and after treatment.

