*Clinical assessments* will include (1) the MINI to clarify psychiatric inclusion and exclusion criteria; (2) the Antidepressant Treatment History Form (ATHF) to clarify on inclusion and exclusion criteria [26]; (3) the SSI will be administered at screening, baseline, weekly, and after treatment to confirm eligibility and to assess changes as a secondary outcome measure; (4) the HRSD-24, which will assess changes in depressive symptoms and will be administered at the baseline and after treatment; (5) the Young Mania Rating Scale (YMRS), which will be used to evaluate mania/hypomania symptoms at screening and throughout the study for eligibility and safety monitoring purposes [27]; and (6) World Health Organization Disability Assessment Schedule (WHODAS 2.0), which will be used as a standard measure of disability promoted and used at baseline and after treatment to assess changes in individual level of functioning [28].

*Neurophysiological assessments* will include (1) the Transcranial Magnetic Stimulation Adult Safety Screen to assess potential TMS risk factors; and (2) TMS-EMG/EEG. Our neurophysiological measures have been established and have a high test-retest reliability (ie, intraclass correlation >0.9) [18,19]. Data analysis will be performed using semiautomated methods developed and validated by our group [29]. TMS pulses will be administered to the left dorsolateral prefrontal cortex using a 7-cm figure-of-eight coil and 2 Magstim 200 stimulators (Magstim Company Ltd) connected via a BiStim module, and motor-evoked potential data will be collected using commercially available software (Signal; Cambridge Electronics). Each TMS session will include the establishment of the individual threshold for stimulation of motor cortex, and dorsolateral prefrontal cortex localization will be performed according to previously published methods [29,30]. The resting motor threshold will be determined by applying single pulses of TMS to the motor cortex while the coil is placed at the optimal position to elicit motor-evoked potentials from the right abductor pollicis brevis muscle. The resting motor threshold is defined as the minimum stimulus intensity that elicited a motor-evoked potential of >50 μV in more than 5 of the 10 trials [30].

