### Statistical Methods

Baseline participant characteristics will be reported and described using summary statistics—mean and SD for continuous data and number and proportion for categorical data. As the primary outcome is to assess feasibility, we will report on (1) recruitment numbers and attrition rates; (2) the number of individuals who experience side effects, and (3) the overall number and type of side effects. For neurophysiology, we will use an independent *t* test (paired 1-tailed) to compare components of TMS-evoked responses in the left dorsolateral prefrontal cortex in TMS-EEG data. In addition, we will apply a nonparametric cluster-based permutation test to investigate any significant changes in overall EEG channels. We will conduct a paired 1-tailed *t* test of the SSI and HRSD-24 scores from baseline to week 4 and monthly follow-up to assess preliminary clinical outcomes. We will also report the standardized mean difference as a measure of effect size (small: 0.2; medium: 0.5; large: 0.8).

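### The SSI is rated weekly, but the only stated SSI analysis compares baseline with week 4 and monthly follow-up, so the week 1–3 ratings enter no stated analysis

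*Protocol article*

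**What the plan says.** **Schedule.** Under Data Collection Methods, "the SSI will be administered at screening, baseline, weekly, and after treatment to confirm eligibility and to assess changes as a secondary outcome measure". The general schedule in the same section collects data at baseline, then "weekly during the course of IV ketamine, within a week after the completion of the intervention, and following 4 weeks for a final follow-up". By the article's own words the weekly SSI scores are outcome data, not only safety checks.

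**Analysis.** Statistical Methods gives one analysis for the SSI: a paired one-tailed t "test of the SSI and HRSD-24 scores from baseline to week 4 and monthly follow-up", with a standardized mean difference as effect size. No other SSI analysis is stated.

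**Rationale.** The abstract says that ketamine "has been shown to have rapid antisuicidal effect and antidepressant qualities, and is thus a promising intervention to target acute suicidality". Background and Rationale says that "there is an urgent need to develop robust interventions to treat suicidality in patients with BD rapidly", and contrasts ketamine with treatments that can take months to work.

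**Rank.** The Outcomes section places acute suicidality among the tertiary outcomes, while Data Collection Methods calls the SSI a secondary measure. The two labels should be reconciled. On either label it is not the primary outcome.

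**The concern.** The case for the drug is that it works fast, and the trial collects data that bear on this. Yet the first SSI comparison comes at the end of a four-week course of eight infusions. A change from baseline to week 4 looks the same whether it happened in the first week or the last. The clinical outcomes are meant to inform a larger trial, and the timing of change is something that trial's designers would want to know.

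The second issue is who is counted. The Discontinuation Criteria remove participants for marked worsening of depression, for hospitalisation because of suicidality, and for missed treatments. If they are not rated at week 4, a paired test leaves them out even though earlier SSI scores exist. They are likely to be among those who did worst, so the mean change in the remainder may look too favourable.

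**Working it through.** The main check sets the schedule against the analysis. The arithmetic only sizes the point. There is no plan figure to reproduce for it: the Sample Size section gives 30 for safety and feasibility, without alpha, power, effect size, SD or dropout.

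**1. Ratings collected and ratings used**
- Post-baseline SSI ratings per person: weeks 1, 2, 3 and 4, plus follow-up, make 5. If the rating within a week of completion is separate from week 4, there are 6. The article does not say which.
- The stated tests use 2 of them: 2/5 = 40% or 2/6 = 33%.
- Ratings at weeks 1–3 in no stated analysis: at most 30 × 3 = 90.

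**2. What week 1 can show**
- Eight infusions over four weeks is two per week, so the first weekly rating follows about two infusions. The article does not say whether it comes before or after that week's second infusion.
- It therefore bears on change within about a week, not within hours or a day.

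**3. Precision of a week-1 contrast**
- 95% CI half-width in units of the SD of change: t(0.975, n−1)/√n. For n = 30 this is 0.373.
- The formula depends on n alone, so week 1 and week 4 are equally precise at equal n.
- Power of a paired one-tailed t test at n = 30 (noncentral t, 29 df), using the article's own effect-size benchmarks. Alpha is not stated, so two values are assumed:

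| d | alpha 0.05 | alpha 0.025 |
|---|---|---|
| 0.2 | 0.28 | 0.18 |
| 0.5 | 0.85 | 0.75 |
| 0.8 | >0.99 | 0.99 |

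These hold equally at week 1 and week 4, so sample size is no reason to leave week 1 out.

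**4. Why not simply add weekly t tests**
- Five unadjusted tests at 0.05, if independent: 1 − 0.95⁵ = 0.23 family-wise error, against 1 − 0.95² = 0.0975 for two.
- With Bonferroni over five tests (alpha 0.01), power at d = 0.5 falls from 0.85 to 0.61.
- One model with a few pre-named contrasts, reported as estimates, is the better course.

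**5. Possible size of the early-leaver effect**
- Let q be the share without a week-4 rating, and g the gap in mean improvement between those with and those without one. The change in the paired set exceeds the change in everyone by q × g.
- The article gives neither figure. Assume q = 15% to 25%, and g = 0.5 or 0.8 SD of change (borrowing the article's medium and large benchmarks as sizes for the gap).
- g = 0.5: 0.15 × 0.5 = 0.075 to 0.25 × 0.5 = 0.125 SD.
- g = 0.8: 0.15 × 0.8 = 0.12 to 0.25 × 0.8 = 0.20 SD.
- On these assumptions the distortion is smaller than the half-width in step 3, but it runs in one direction.

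**The case against.** The strongest reply is that this is a condensed article on a pilot whose primary outcome is safety and feasibility. It does not say that weeks 1–3 will be ignored, and a SAP or full protocol may use them. No objective asks about speed of onset, and the end of an eight-infusion course is a natural time to assess a repeated-dose treatment. Dose adjustment is expected in the first one to three sessions, so week 1 falls while doses are still being set. An unstructured covariance over 6 or 7 occasions, baseline included, needs 6 × 7/2 = 21 or 7 × 8/2 = 28 parameters from 30 people.

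Much of this stands. It limits the weight of the point and shapes the fix. It does not remove the point, because the article goes beyond silence: it names a method and its time points, and that method cannot use the weekly scores that the article says are taken to assess change.

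Three stronger readings are tempting and are not supported:
- **That the trial throws the weekly data away.** The data are collected and kept. They are only absent from every analysis stated here.
- **That week 1 would separate a drug response from ordinary remission where week 4 cannot.** The trial has one arm and selects on an SSI of 9 or higher. Regression to the mean, expectancy and natural remission affect week 1 too. The article's Limitations already concede the lack of a control group.
- **That week 1 is more precise.** With 15% to 25% lost by week 4 (26 to 23 pairs), the week-4 half-width would be 0.404 to 0.432 SD against 0.373. That gap comes wholly from assuming loss at week 4 and none at week 1.

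**Conclusion.** The concern holds, limited to the SSI; the HRSD-24 is listed only at baseline and after treatment. The stated SSI analysis uses 2 of 5 or 6 post-baseline ratings and omits the three that bear on early onset, although speed is the reason given for the treatment. It also drops anyone without a week-4 rating from the week-4 comparison. On assumed loss and response gaps this could overstate the change by about 0.08 to 0.20 SD.

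This rests on reading week 4 as the end of the course, and on discontinued participants not being rated at week 4, which the article does not settle. The primary safety and feasibility conclusions are unaffected. The change is worth making because it needs no new data, but the trial does not fail without it.

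**What to change.** Replace the SSI paired t tests with one mixed model for repeated measures:
- **Response:** baseline and all post-baseline SSI ratings, with visit as a factor. State whether week 4 and the post-treatment rating are the same visit.
- **Covariance:** a parsimonious structure suited to about 30 participants. A first-order autoregressive form with visit-specific variances, for example, needs 7 or 8 parameters for 6 or 7 occasions.
- **Contrasts:** pre-name baseline to week 1 as the early change, and keep week 4 and follow-up as later contrasts. Report each with a 95% CI and describe all as exploratory.
- **Participants:** everyone with a baseline and at least one later SSI. State that the model relies on data missing at random given the earlier ratings, which early leavers may not satisfy fully.
- **Interpretation:** say that the early contrast describes timing within about a week and does not isolate a drug effect.

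The cost is slightly more modelling and a change of analysis text, with no extra visits, ratings or participants. The article reports that 5 participants had already completed this open-label trial, so the early contrast would be named after some outcomes could be known to the team. The amendment should disclose this.

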### Monitoring

#### Trial Monitoring

We will perform internal quality management of study conduct, data collection, documentation, and completion through proactive study monitoring using our team-based monitoring approach. Monitoring will be conducted prior to, during, and after the study concludes to ensure that good clinical practice is maintained. All data monitoring, auditing, and harms reporting will be performed according to CAMH Research Ethics Board and regulatory standards. The study investigator and delegated research personnel will monitor study participants according to the study protocol and continually assess the patient for adverse outcomes; all adverse events will be assessed in real-time to determine if they meet the criteria for a “serious adverse event” and how the event was “related” to the study intervention.

#### Harms

Adverse events occurring as of the first administered dose of the investigational product and 30 days after the last administered dose will be collected. All reported adverse events will be followed up to the resolution, or an appropriate posttrial follow-up plan will be determined. Serious unexpected adverse drug reactions will be reported as required by Health Canada, the Food and Drug Regulations—Division 5. For this pilot trial, all relevant adverse events and all serious adverse events will be reported to the Research Ethics Board directly if they meet applicable reporting requirements.

#### Auditing

At the time of this publication submission, the study also passed the CAMH Quality Assurance internal auditing process. Quality control procedures will be implemented beginning with the data entry system, and data quality control checks that will be run on the database will be generated. Any missing data or data anomalies will be communicated for clarification/resolution.

### Research Ethic Approval

This study has received CAMH Research Ethics Board (approval number 179-2020) and Health Canada (approval number NOL251577) approvals.

### Consent

We will obtain informed consent from each participant who agrees to participate in the trial. Patients meeting the criteria will be referred to the research analyst/study coordinator to discuss the study purpose, procedures, potential risks, and rights as research participants. Consent forms describing the study intervention, study procedures, and risks will be given to each participant, and written documentation of informed consent will be required prior to completing the initial screening visit and starting the study intervention. Once consent is obtained, the research personnel will confirm that inclusion and exclusion criteria are met before proceeding with baseline testing. Patients will be informed that they can withdraw participation at any point during the study. The participants will be given a copy of the information and consent documents for their records. The informed consent process will be documented, and the form will be signed before the participant undergoes any study-specific procedures. The rights and welfare of the participants will be protected by emphasizing that the quality of their medical care will not be adversely affected if they decline to participate in this study (Multimedia Appendix 3).

### Confidentiality

Data confidentiality and confidentiality of the identities of the individuals participating in this study will be strictly maintained. Data forms that include identifying information will be kept in locked cabinets. Only the unique ID number assigned by the research coordinator will be used to represent participants during data entry, data transfer, data analysis, or other file management procedures. All information linking their identity will be kept separate from the research records. All information entered into a computer will be stored in a password-protected and encrypted file format on a secure server. If any participant withdraws from the study, any research information recorded for or resulting from the participant prior to the date that the participant formally withdrew consent will continue to be stored and used (in the manner described above) for research purposes (and will be disclosed by the investigators); however, no new data will be collected. Withdrawing from the study will not have any consequences for the participant. Participants’ identities will not be revealed in the publication or presentation of any results from this study.

### Access to Data

The data sets generated during and/or analyzed during this study are not currently publicly available due to the ongoing trial but will be available from the corresponding author upon reasonable request.

### Dissemination Policy

The results of this study will be disseminated through publications and presentations at the scientific conferences.

## Results

This study is currently ongoing and actively recruiting participants. So far, 5 participants have completed the trial, 1 is currently in active treatment, and 8 participants are on the waitlist to be screened. We anticipate initial results being available in the fall of 2023. This proposal was presented as a poster presentation at the Research to Reality Global Summit on Psychedelic-Assisted Therapies and Medicine, held in May 2022 in Toronto, Canada.

## Discussion

### Expected Findings

Developing effective interventions for acute suicidality in high-risk populations such as BD remains a major therapeutic challenge. Ketamine, an NMDA receptor antagonist, represents a promising intervention due to its rapid antidepressant and antisuicidal effects [11]. However, our understanding of its underlying neurophysiological mechanisms for suicidality in BD is limited. TMS-EMG and TMS-EEG can be used to produce a reliable neurophysiological measure of NMDA receptor–mediated neurotransmission [15]. To our knowledge, this is the first study to investigate the safety/feasibility and neurophysiological changes of repeated 40-minute ketamine infusions to treat suicidality in patients with BD. Results from this study will (1) inform the development of a larger, adequately powered randomized controlled trial to test the feasibility of a series of IV ketamine infusions to treat suicidality in patients with BD and (2) determine potential neurophysiological markers of clinical response.

### Limitations

In general, a lack of a control group and a small sample size are limitations in ketamine clinical trials. However, given that this is a pilot open-label clinical trial, the sample size is sufficient (ie, the goal is not to assess generalizability or statistical significance). The lack of blinding in the control group is a common concern in ketamine trials because a placebo with comparable effects does not exist, and it is impossible to ensure blinding to the full extent. Because the study is conducted at a single site of a large psychiatric academic facility, the results may not be fully transferable to a broader population; however, the study will provide preliminary data on feasibility and safety to be used in a larger, adequately powered and controlled trial. Moreover, a small sample size may not allow drawing any meaningful conclusions around neurophysiological markers of response; however, results will inform a further larger clinical trial where we can test neurophysiological markers more accurately.

